## Abstract

**Background:**

Several food and nutrition education actions have been described in the literature, with emphasis on the recommended use of innovative methods when addressing a young audience. Digital games are an attractive, dynamic, and motivating resource for teaching and learning practices, and adolescents form the group that readily accepts and adopts new technologies. Adapting dietary and nutritional guidelines to change dietary behavior is a challenge, and game-based learning has several benefits that can be used in this sense. Thus, this study aims to outline a nutritional intervention for school-aged adolescents from the Federal District, Brazil, whose object is a digital card game aimed at promoting healthy dietary practices.

**Methods:**

In this randomized study with intervention and control groups, we propose a nutritional intervention for adolescents studying in Federal District private schools. The intervention group will be introduced to *Rango Cards*, a digital game specifically developed for this study. The purpose of the game is to present the concept of an adequate and healthy diet using simple information in a playful context. This game features cards for foods/meals, characters, and healthy habits. The players’ choices may lead them to winning or losing. Theme selection and phase order were designed to provide a learning experience. The control group will not receive any material during the study. Both groups will complete questionnaires before and after the intervention. The game is expected to improve food knowledge and self-efficacy in the adoption of healthy practices, thus contributing to appropriate dietary consumption.

**Discussion:**

The game was designed as a food and nutrition education tool based on Brazilian dietary guidelines. We believe that *Rango Cards* will provide a comprehensive experience on the topic, improving the students’ autonomy, motivation, and pleasure of learning.

**Trial registration:**

RBR-72zvxv June 29, 2018; Retrospectively registered.

## Background

Obesity is a serious public health problem that affects different age groups worldwide. Surveys on health and nutritional status of Brazilian students have shown an exponential growth in the prevalence of overweight and obesity in recent decades [1–3]. This situation has important health implications [4] and results from multiple factors, including modifiable conditions such as an inadequate diet. As the literature clearly demonstrates, the high consumption of ultra-processed foods correlates with the prevalence of overweight and obesity among adolescents and adults [5–10].

The dietary practices of Brazilian adolescents are frequently considered inappropriate because they include regular intake of soft drinks, artificial juices, sweets, sugar, and fried and high-fat foods; low intake of fruits and vegetables; and irregular eating habits, as meals are replaced with snacks and breakfast is missed [1–3, 11–13]. The Brazilian Study of Cardiovascular Risks in Adolescents (ERICA), with 71,791 participants, reported that the consumption of saturated fats, sugar and sodium was higher than the recommended upper limits; conversely, the recommended consumption of calcium and vitamins A and E was not reached [14].

Coping with that public health issue is a major challenge because eating behavior is influenced by the dietary environment and by social, cultural, and infrastructure conditions [15]. Current World Health Organization (WHO) guidelines indicate that a set of regulatory provisions, educational actions, and breastfeeding and healthy diet measures should be adopted to prevent obesity in children and adolescents [16].

Dietary guidelines are food and nutrition education (FNE) tools aimed at promoting healthy lifestyles and preventing diet-related diseases at the individual and collective level [17]. In Brazil, the *Dietary Guidelines for the Brazilian Population* provide a framework for educational actions, and their implementation should be based on the use of methods that encourage people to discuss and understand the concepts involved in eating behavior [18, 19]. To disseminate their content, some aspects should be considered, including the social market and the available technological innovations [20], such as the Internet and mobile devices (tablets and smartphones) [21].

Mobile health (mHealth) integrates mobile technology with public health practices with the purpose of improving communication and achieving healthy lifestyles [22]. Studies have reported that mHealth interventions may increase access to health care services; initiate the process of behavior changes or increase motivation for small changes; and spread knowledge, especially if aimed at receptive consumers [23–26]. Adolescents and young adults form the audience that readily accepts and adopts new technologies; thus, the diffusion effect may be stronger among them [27].

When assessing behavior changes in the field of food and nutrition, another important term is mobile nutrition, or mNutrition. This type of technology is based on repeated contact and exposure to messages that increase knowledge and raise awareness about nutrition, being a useful tool to change attitudes and support healthier lifestyles in terms of dietary habits [28, 29].

Currently, there is consistent evidence of the benefits of using mobile tools to improve health behaviors, especially when they are developed within a theoretical framework [30]. According to Sparapani [31], social cognitive theory [32] can be applied in health promotion to link interactive technologies and behavior changes. However, studies assessing the effectiveness of such interventions are still scarce [29, 33], requiring further research [34, 35]. Recently, Melo et al. [30] systematically reviewed 11 studies on the use of technologies in nutritional interventions for adolescents. The authors suggest that long-term interventions tend to be more successful when they involve frequent exposure to technological resources and a theoretical component aimed at a single health behavior change. The most commonly used theoretical framework in the reviewed studies was social cognitive theory.

mHealth strategies include the use of mobile applications (apps) as a resource for health improvement [36]. These mHealth apps have been increasingly downloaded [37], including digital games [38, 39]. In their review, Melo et al. [30] indicated that games seem to be promising tools for nutritional interventions, as all reviewed studies using this type of technology were effective, especially among young people.

Games are interactive systems that allow a more flexible relationship with the content, thus the player takes the leading role in the learning process. Their potential contribution depends on the player’s comprehension of the concept of the game and on the process of game design and its consequences [40, 41]. Schell [40] says that interactivity is a key element to understand the game. Without its interactive nature, the game becomes a linear narrative, similar to videos or books [42].

To be an engaging learning experience, the game must have the following attributes: gameplay, rules, goals, interactions, adaptations, actions, feedback, winning, conflicts, resolutions, and interpretations, all of them working interconnected [39]. Games designed to improve people’s cognitive and intellectual skills [43] are called educational games, learning games, or serious games [38, 44]. Several benefits have been attributed to game-based learning [43, 45, 46], including changing people’s behavior [44, 47], which justifies its increasing importance in the game industry [48].

To actually play the game, the player must be driven by an intrinsic motivation, i.e., the sense of pleasure generated by the interaction [49]. The fascinating feature of the game is responsible for conducting the player’s experience in the universe of the game. The boundary between the game world and the real world is called the magic circle [50]. Because the act of staying in the magic circle is voluntary, the game must be designed to provide a comprehensive experience [51], in a process known as game design.

Game design is the art of organizing and aligning the different elements that form a game, which are known as the elemental tetrad and include story, aesthetics, mechanics, and technology [40]. With respect to the game mechanics, the process of learning how to play the game should provide the intended knowledge and skills [52]. The player’s immersion is based on the process of regulation of the difficulty level presented by the game [40, 42, 53]; thus, hard games may cause frustration while very easy games may be tedious [54]. Regarding the story, there is a strong need to plan a transversal progression throughout the game [55], which allows a fluid immersion of the player in the magic circle.

Several FNE actions have been described in the literature; however, the challenge of adapting food and nutrition guidelines to achieve effective changes in health behavior remains [12], especially when involving the adoption of innovative methods of health education [56]. Digital games have the potential to support the learning process, providing greater personalization, dynamism, and autonomy. They are considered promising tools to promote changes in dietary behavior, which is the scope of this study.

Therefore, this study aims to outline a nutritional intervention for school-aged adolescents from the Federal District, Brazil, whose object is a digital game aimed at promoting healthy dietary practices. It is randomized study with intervention and control groups.

## Methods

### Study design

This protocol describes the development of a game-based nutritional intervention to implement the *Dietary Guidelines for the Brazilian Population* [19] among Federal District students. A randomized study with intervention and control groups will be conducted. The study was approved by the Research Ethics Committee of the University of Brasília School of Health Sciences (protocol no. 53175015.6.00000030) and funded by the Research Support Foundation of the Federal District, Brazil (FAPDF). The school units, the students, and their parents or legal guardians will provide written consent before the beginning of the study. We intend to visit each school unit at least three times during the study.

### Participants

#### Eligibility criteria

The studied population will consist of 1st-year high school students from private Federal District schools [57]. We chose private schools because the intervention involves a digital game that will be installed in student-owned mobile devices (smartphones and tablets), which tend to be expensive and thus more accessible to private school students than public school students. This study has no exclusion criterion.

#### Sample size and recruitment

The sample size was calculated considering the prediction of a 1.5 point increase in the food knowledge score after the intervention, with a standard deviation of 2.9 [58], a significance level of 5%, and power of 80%. Under these conditions, the minimum sample should be of 60 individuals per group, with control of the participants’ gender. Adding an estimated 40% loss between the pre- and post-intervention moments, the minimum total sample is defined as 168 individuals (84 per group). Each class in private schools has approximately 35 students [57]. Considering an estimate enrollment of 21 participants per class (40% of refusal), we expect to enroll 8 schools in the study, which will be randomly selected to form the study groups: 4 in the intervention group and 4 in the control group.

To recruit the selected school units, we will use email, telephone, and in-person visits to contact each school and explain our research. After the schools agree to participate and sign a consent form, we will select 1st-year high school classes and schedule visits to explain the study to students. Those who verbally agree to participate will be asked to request the written consent of their parents or legal guardians. Finally, the students’ assent will be obtained. Figure 1 shows the flowchart of recruitment and intervention of the study.

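### The 80% power was calculated for independent, individually randomised students, with no design effect, although eight schools (four per group) are allocated

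*Protocol article*

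**What the plan says.** Everything needed is in the Sample size and recruitment section of the protocol article.

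- The target is the "prediction of a 1.5 point increase in the food knowledge score after the intervention". The assumed spread is given as "with a standard deviation of 2.9", and the error rates as "a significance level of 5%, and power of 80"%.
- From this, "the minimum sample should be of 60 individuals per group".
- The loss allowance follows: "Adding an estimated 40% loss between the pre- and post-intervention moments, the minimum total sample is defined as 168 individuals (84 per group").
- Recruitment is by school: "Considering an estimate enrollment of 21 participants per class (40% of refusal), we expect to enroll 8 schools in the study". It is then the schools, not the students, that are divided between the groups: "which will be randomly selected to form the study groups: 4 in the intervention group and 4 in the control group".

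No ICC, design effect or other allowance for school is stated. The Intervention group section adds a competition among the students of each school. The Data analysis section names an unpaired Student's t-test for food knowledge and self-efficacy, the two primary outcomes, and mentions no school term.

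**The concern.** The sample size treats students as independent, while the allocation puts all participants of a school in the same group. Students in one school share teachers, peers and background, and here also a within-school contest, so their scores are likely to be correlated. Two things then reduce the information: the correlation itself, and the fact that a comparison of four schools with four has only 8 − 2 = 6 degrees of freedom. Neither enters the calculation.

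What is at stake depends on the analysis. With a valid school-level analysis, the trial has less chance of detecting its own target effect than it claims, and a null result could be misread as evidence against the game. With the student-level t-test that the article names, the 5% significance level is not held, and a false claim that the game works becomes more likely.

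**Working it through.** **Inputs from the Sample size and recruitment section.** Difference 1.5, SD 2.9, significance level 5% (two-sided reproduces the stated figure; one-sided gives 47), power 80%, 40% loss, 21 enrolled per class, eight schools. **Assumed, because the article gives no value:** ICC 0.02, 0.05 and 0.10. **Inferred:** one class per school, since 8 × 21 = 168.

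**1. The stated figure.** n per group = 2(1.960 + 0.842)² × 2.9² / 1.5² = 58.7, so 59 by the normal formula. The exact t-test needs 59.65, so 60. Power is 0.802 at 60 and 0.796 at 59. The 60 is reproduced with a design effect of 1, and no room is left for a larger one.

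**2. The loss allowance, apart from clustering.** 60 × 1.4 = 84, but 84 × 0.6 = 50.4 completers. For independent students that gives about 73% power. Keeping 60 completers would need 60 / 0.6 = 100 enrolled per group.

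**3. Students per school.** Enrolled: 168 / 8 = 21. After 40% loss: 21 × 0.6 = 12.6. To give the stated 60 per group: 60 / 4 = 15.

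**4. Power with four schools per group.** With m students per school:

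- design effect DE = 1 + (m − 1) × ICC
- SE = 2.9 × √(2 × DE / (4m))
- power from the noncentral t distribution with 6 df and noncentrality 1.5 / SE

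| m per school | ICC | DE | SE | Power for 1.5 points |
|---|---|---|---|---|
| 12.6 (after 40% loss) | 0.02 | 1.23 | 0.641 | 50% |
| 12.6 | 0.05 | 1.58 | 0.726 | 41% |
| 12.6 | 0.10 | 2.16 | 0.849 | 32% |
| 15 (stated 60 per group) | 0.02 | 1.28 | 0.599 | 56% |
| 15 | 0.05 | 1.70 | 0.690 | 45% |
| 15 | 0.10 | 2.40 | 0.820 | 34% |
| 21 (no loss) | 0.02 | 1.40 | 0.529 | 66% |
| 21 | 0.05 | 2.00 | 0.633 | 51% |
| 21 | 0.10 | 3.00 | 0.775 | 37% |

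Outside these ICCs, with 12.6 completers: 59% at ICC 0, 54% at 0.01 and 23% at 0.20. A normal approximation, which ignores the 6 df, gives 69%, 65%, 54% and 42% at ICC 0.01, 0.02, 0.05 and 0.10.

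**5. Detectable difference at 80% power.** With 6 df this is 3.367 × SE. For 12.6 completers: 2.2, 2.4 and 2.9 points at the three ICCs, against the planned 1.5.

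**6. Student-level t-test ignoring school.** Its type I error is about 2 × [1 − Φ(1.96 / √DE)]. For 12.6 completers: 7.7%, 11.9% and 18.2% at the three ICCs.

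**7. Schools needed for 80%.** With k schools per group, 12.6 completers each, 2k − 2 df and no baseline adjustment, the smallest k is 7 (power 81%), 9 (83%) and 12 (83%) at ICC 0.02, 0.05 and 0.10.

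**The case against.** **The ICC may be in the full protocol or the analysis plan.** An article does condense. But the published 60 already equals the unclustered figure, so a design effect cannot have been applied to it elsewhere. This objection falls.

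**A reader might infer that the true power is 30–50%.** The documents do not support that as a fact. The range holds only for ICCs of about 0.02 to 0.11, with 12.6 completers per school and a test on 6 df. A smaller ICC, less loss or a normal approximation gives higher figures; a larger ICC gives lower ones. This objection stands, and every power figure must carry its conditions.

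**Not all of the shortfall is clustering.** This stands. Steps 2 and 4 separate the parts: the loss allowance alone brings 80% down to about 73%, and the rows for 15 and 21 students per school show what clustering and few schools do without that error.

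**The article does not plan a school-level test.** This stands too. Under the planned t-test the chance of a significant result for a 1.5-point effect stays at about 67–72% for ICC 0.02 to 0.10, but only because the test no longer works at 5%. The main harm is then false positives.

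**One class per school is an inference.** The article calls 168 a minimum and speaks of selecting classes in the plural. Two classes per school (25.2 completers), treated as one cluster, would give about 71%, 54% and 39%, still below 80%.

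**Conclusion.** The point holds in conditional form. The calculation and the allocation, in one paragraph, describe different designs: "8 schools in the study, which will be randomly selected to form the study groups", yet the 60 per group assumes independent students. With the 12.6 completers per school that the article's own loss rate implies, power for 1.5 points on a school-level test is below 80% at every ICC tried, including 59% at zero. At assumed ICCs of 0.02, 0.05 and 0.10 it is about 50%, 41% and 32%. If school is ignored instead, the type I error is about 8%, 12% and 18%. Either way, the stated pair of 5% significance and 80% power is not a property of this design.

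The figures rest on the assumed ICCs, on one class per school and, for power, on 6 df. No single value can be called the real power, and the figures for 12.6 completers include the separate loss-allowance error. The step from 1.5, 2.9, 5% and 80% to 60 is itself arithmetically right for the model it uses.

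**What to change.** In Sample size and recruitment, restate the power and the detectable difference for four schools per group, the expected completers per school, a stated ICC range and 6 df. State the number of classes per school, and show the loss allowance separately (84 enrolled leaves 50.4 completers per group).

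Base these figures on an analysis that accounts for school, for example a comparison of the eight school means, and put it in Data analysis in place of the unclustered t-test.

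Do not claim 80% power for eight schools. If 80% is to stay, name the number of schools it needs: about 7, 9 or 12 per group at ICC 0.02, 0.05 or 0.10, with 12.6 completers each and no adjustment.

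Quote a gain from baseline adjustment only if that analysis is adopted and 2.9 is confirmed as the SD of the score, not of its change. The article speaks of an increase and leaves this open, and an SD of change would count the gain twice.

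Cost: restating needs only wording and no extra students, but the stated power becomes less favourable. Keeping 80% costs additional schools.

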#### Data analysis

After data collection, the questionnaires will be entered into electronic spreadsheets. To ensure data reliability, data will be double entered. Sociodemographic variables will be analyzed descriptively and expressed as mean, standard deviation, and frequencies. The Pearson’s chi-squared test will be used for sex and age, while the Mann-Whitney U test will be used for family income and maternal level of education. To assess the impact of the intervention, unpaired analyses will be performed using the Student’s t-test for continuous numerical variables (dietary perceptions) and Likert-type scales (food knowledge and self-efficacy). The Mann-Whitney U test will be used for dietary practices and food consumption. The significance level will be set at 5%, and the statistical analyses will be performed using the Statistical Package for the Social Sciences (SPSS), version 21.0.

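### The sample size is stated to be with control of gender, but its listed inputs contain no sex term and the planned t-test of the primary outcomes cannot control for sex

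*Protocol article*

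**What the plan says.** All of the relevant text is in the Methods of the protocol article.

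- **Sample size and recruitment, inputs.** The calculation rests on the "prediction of a 1.5 point increase in the food knowledge score after the intervention", "with a standard deviation of 2.9", and "a significance level of 5%, and power of 80"%. It concludes that "the minimum sample should be of 60 individuals per group, with control of the participants’ gender".
- **Sample size and recruitment, allocation.** Eight schools are expected, "which will be randomly selected to form the study groups: 4 in the intervention group and 4 in the control group". The article mentions no balancing of the arms by sex.
- **Game components (closing paragraph).** The primary outcomes are food knowledge and self-efficacy.
- **Measures.** Sex is collected in the pre-intervention questionnaire.
- **Data analysis.** "To assess the impact of the intervention, unpaired analyses will be performed using the" Student's t-test for food knowledge and self-efficacy. Sex appears once in this section, among the sociodemographic variables: the Pearson "chi-squared test will be used for sex and age".

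**The concern.** The plan claims a property, control of gender, that its stated primary analysis does not have. A two-sample t-test compares two means and has no place for a covariate. The chi-squared test on sex can show that the arms differ in sex mix, but it does nothing to the estimated effect.

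Two things are at stake. First, a reader of the sample size section would believe that the primary comparison takes sex into account, when the analysis section shows that it does not. Second, if sex predicts the score, any difference in sex mix between the arms is carried into the unadjusted difference in means. Such a difference can arise by chance, with only four schools per arm. It could also arise through refusal or loss that depends on sex. The plan expects 40% of each, and only one arm is asked to play a competitive game.

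**Working it through.** **1. Reproduce the plan's figure.** Inputs from Sample size and recruitment: difference 1.5, SD 2.9, 5% (sidedness not stated), power 80%.

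- Two-sided normal approximation: n = 2 × (1.960 + 0.842)² × (2.9/1.5)² = 58.7, so 59 per group.
- Two-sided exact t-test (noncentral t), effect 1.5/2.9 = 0.517: n = 59.65, so 60 per group. Power at 60 is 80.2%.
- One-sided normal approximation: 47, which does not match.

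The stated 60 is therefore the ordinary two-sided two-sample figure, and no sex input is needed to obtain it.

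**2. Would a sex covariate have changed the number?** Use a residual SD of 2.9 × √(1 − R²) and 2n − 3 degrees of freedom, where R² is the assumed share of variance explained by sex:

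| Assumed R² | n per group for 80% | Power at 60 |
|---|---|---|
| 0 | 60 | 80.2% |
| 0.01 | 60 | 80.6% |
| 0.02 | 59 | 81.0% |
| 0.05 | 57 | 82.2% |
| 0.10 | 54 | 84.2% |

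A weak sex covariate also gives 60, so the number cannot show whether sex was considered. It can only be said that no sex input is listed.

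**3. Could the phrase mean adequate size within each sex?** With 30 per sex per group, power within one sex is about 50% (t-test). Reaching 80% within each sex would need about 60 per sex per group, or 120 per group. That reading does not fit 60.

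**4. Size of the effect on the estimate.** The documents give neither a sex gap nor a sex mix, so these are assumptions: a gap of 0.3 to 0.5 SD, which is 0.3 × 2.9 = 0.87 to 0.5 × 2.9 = 1.45 points. Shift = difference in share of girls × gap. Standard error at 60 per group = 2.9 × √(2/60) = 0.53.

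| Difference in share of girls | Shift (points) | Share of 1.5 | Shift / SE |
|---|---|---|---|
| 10 points | 0.087 to 0.145 | 6 to 10% | 0.16 to 0.27 |
| 20 points | 0.174 to 0.29 | 12 to 19% | 0.33 to 0.55 |

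**5. How likely is such an imbalance by chance?** Assume half girls overall, 21 × 0.6 ≈ 13 completers per school and four schools per arm. Simulated probabilities:

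| Between-school SD of share of girls | Arms differ by ≥ 10 points | Arms differ by ≥ 20 points |
|---|---|---|
| 0 | 28% | 4% |
| 10 points | 37% | 9% |
| 15 points | 45% | 15% |

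**6. Gain in precision.** With equal numbers of each sex, R² = 0.25 × gap². This gives 0.25 × 0.3² = 0.0225 to 0.25 × 0.5² = 0.0625, and power at 60 per group moves from 80.2% to 81.1 to 82.7%.

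**The case against.** The phrase is ambiguous. It stands in a sentence about the sample and may mean watching the sex mix at recruitment or checking the groups for comparability, which the chi-squared test would do. The article never says in terms that the primary comparison is adjusted for sex. This is also a condensed article, and the recruitment flow figure is not shown, so its silence about balancing the allocation by sex proves little. That stands: the point should not rest on the allocation. It rests on the test, which the article does state. Even on the comparability reading, a descriptive check is not control.

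The second objection is that the harm is small and assumed. This also largely stands. When sex mix does not cluster by school, variation due to sex is already part of the outcome SD, so the t-test's standard error covers chance imbalance. The higher probabilities in the simulation come from clustering of sex within schools. That belongs to the separate matter of allocating schools and analysing individuals, which a sex term would address only in part.

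A reader might infer that 60 is the wrong number, or that the primary effect will be biased by sex. The documents support neither. A model with a weak sex covariate gives 60 as well, chance imbalance is random error, and nothing in the article indicates the direction or size of any sex-selective refusal or loss.

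**Conclusion.** The point holds in a limited form. The sample size section states control of gender; the listed inputs contain no sex term, and the stated test of both primary outcomes cannot provide that control. This follows from explicit text and needs no assumption beyond the ordinary meaning of control.

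The practical consequence is probably small. A 10-point imbalance shifts the estimate by about a sixth to a quarter of a standard error, and a 20-point imbalance by at most about half of one. Both figures depend on an assumed sex gap of 0.3 to 0.5 SD; if sex does not predict the score, the shift is zero. The gain in power from adjustment is one to three percentage points. The remaining reasons to act are that the plan should do what it says, and that adjustment gives some protection if refusal or loss depends on sex differently in the two arms.

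**What to change.** In Data analysis, replace the unpaired t-test for food knowledge and self-efficacy with a linear model that contains group and sex. Fix sex as a covariate in advance, whatever the chi-squared test shows, and use it alongside any other adjustment adopted, such as baseline score or school. A model with group and sex alone should not be fixed as primary if those other adjustments are also taken up.

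If the unadjusted t-test is kept, remove the reference to gender control from Sample size and recruitment and state that both the sample size and the test are unadjusted for sex.

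The cost is one sentence in the analysis section, one model term and one degree of freedom. Sex is already collected at the first questionnaire, so no students, visits or measures are added, and 60 per group need not change.

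### The 40% loss is added as 60 × 1.4 = 84 per group instead of 60 / 0.6 = 100, so the stated minimum sample gives about 73% power, not 80%

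*Protocol article*

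**What the plan says.** All of this stands in one paragraph of the protocol article, under *Sample size and recruitment*. The target is "the prediction of a 1.5 point increase in the food knowledge score after the intervention", "with a standard deviation of 2.9", at a 5% significance level and 80% power. From these inputs the article concludes that "the minimum sample should be of 60 individuals per group".

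It then allows for attrition: "Adding an estimated 40% loss between the pre- and post-intervention moments, the minimum total sample is defined as 168 individuals (84 per group").

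Recruitment is sized to that total. Classes have about 35 students. "Considering an estimate enrollment of 21 participants per class (40% of refusal"), the article expects to enrol eight schools, four per group.

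Under *Data analysis*, food knowledge is to be compared between groups by an unpaired method: "unpaired analyses will be performed using the Student’s t-test". At the end of *Game components*, food knowledge is named as one of the two primary outcomes.

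**The concern.** The 60 per group is the number that must be available for the comparison after the intervention. The loss is described as occurring between the two questionnaires, so its base is the students enrolled and measured at baseline. To have 60 left after losing 40% of those enrolled, one divides 60 by the retained fraction, 0.60. The article instead adds 40% of 60 to 60, and that does not leave 60 once the loss is taken.

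The plan therefore misses its own minimum under its own loss rate. The stated 80% power for a primary outcome is not delivered, and the error carries through to the number of schools, because the recruitment figures are built to reach 168.

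**Working it through.** **Inputs** (*Sample size and recruitment* unless noted)

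- Difference δ = 1.5 points; SD σ = 2.9; standardised difference d = 1.5 / 2.9 = 0.517.
- Significance level 5%; power 80%.
- Unpaired Student's t-test (*Data analysis*), equal groups.
- Loss between questionnaires: 40%.
- Sidedness is not stated. Two-sided is inferred, because it reproduces the article's 60; a one-sided test gives 47 and a paired design about 32.

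**Step 1. Reproduce the 60 per group.** The normal approximation is

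n = 2(z₀.₉₇₅ + z₀.₈₀)² σ² / δ² = 2 × (1.960 + 0.842)² × 8.41 / 2.25 ≈ 58.7, so 59.

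The t-test solution is 59.65, so 60 per group. Power at 60 is 80.2%. The article's figure is reproduced.

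**Step 2. Reproduce the 84 per group.**

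- n × (1 + loss) = 60 × 1.40 = 84, the article's figure.
- n / (1 − loss) = 60 / 0.60 = 100, the number that leaves 60 after a 40% loss.

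**Step 3. Completers at the stated enrolment.** 84 × 0.60 = 50.4 per group, or 168 × 0.60 = 100.8 in total, against 120 needed.

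**Step 4. Power with those completers** (δ = 1.5, σ = 2.9, two-sided 5%)

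| Completers per group | t-test power | Normal approximation |
|---|---|---|
| 50 | 72.6% | 73.4% |
| 50.4 | 72.9% | 73.8% |
| 60 | 80.2% | 80.9% |

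**Step 5. Difference detectable with 80% power.** The detectable difference scales with 1/√n: 1.5 × √(59.65 / 50.4) = 1.5 × 1.088 ≈ 1.63 points.

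**Step 6. Loss that 84 per group can absorb.** 1 − 60/84 = 24/84 = 28.6%.

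**Step 7. Slack in recruitment.** Refusal is applied to those approached: 35 × 0.60 = 21 per class. With one class per school, 8 × 21 = 168, exactly the stated minimum. At 21 per class, 200 students would need 200 / 21 = 9.5, so 10 classes.

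**The case against.** Several points can be made for the plan.

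- **The 168 is called a minimum.** The article does not fix one class per school, so actual enrolment could exceed 168, and two more classes of 21 would give 210, above the 200 needed. This is true, and the 50 completers therefore apply if only the stated minimum is enrolled and the full 40% is lost. But eight schools at 21 students give exactly 168, no reserve is stated, and a minimum that fails under its own assumptions is still wrong.
- **The loss may be smaller.** The play period is only three weeks, and with loss up to 28.6% the 84 is enough. That is fair, but 40% is the plan's own estimate.
- **The shortfall is moderate.** Power drops by about 7 percentage points and no bias is introduced. This stands. It limits the harm without making the stated figure right.
- **The two 40% figures describe different events**, refusal before enrolment and loss after it. This also stands. The refusal sentence shows the percentage being taken from the correct base, but the error does not depend on that comparison.
- **Sidedness is inferred.** A one-sided test would need only 47 per group, but that contradicts the article's 60.
- **73% is itself optimistic, because schools are allocated.** This is correct as a caution. The article gives no intraclass correlation, so any figure is an assumption. With 50.4 / 4 = 12.6 completers per school, an intraclass correlation of 0.02 gives a design effect of 1 + 11.6 × 0.02 = 1.23 and power of about 65%; 0.05 gives 1.58 and about 54%. Both are normal approximations that ignore the small number of schools. This is a separate defect. It means that 73% must be labelled as the plan's individual-level figure, and that 100 per group would likewise restore 80% only on that basis.

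**Conclusion.** The concern holds. The inflation for loss is arithmetically wrong as written: 84 per group does not keep 60 after a 40% loss. At the stated minimum and the stated loss, about 50 students per group remain. The chance of missing a true 1.5-point difference is then about 27% instead of 20%.

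This rests on a two-sided test, on exactly 168 students enrolled, on the full 40% loss, on students without a second questionnaire not counting towards the 60, and on the plan's treatment of students as independent. Nothing elsewhere in the article repairs the figure. A stated sample size and power for a primary outcome are wrong under the plan's own assumptions, so the sentence must be corrected.

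**What to change.** Correct the loss sentence in *Sample size and recruitment* in one of three ways:

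1. Keep 168 and 40% loss, and state that this leaves about 50 completers per group, with about 73% power for 1.5 points, or 80% power for about 1.63 points.
2. Keep 168 and 80% power, and state that 84 per group covers a loss of up to 28.6%. This needs a reason for expecting less than the 40% now given.
3. Keep both 60 completers and 40% loss, and set the minimum at 100 per group, 200 in total.

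Whichever is chosen, say that the test is two-sided and that the figures treat students as independent, before any allowance for allocation by school.

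The first two cost one corrected sentence and no extra students; the first also means a less favourable stated power. The third costs 32 more students, or 10 classes instead of 8 at 21 per class.
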